## **ABSTRACT**

With suicide prevention as a national priority (1, 2) early suicide detection and intervention programs are being implemented in schools, primary care clinics, and emergency departments (EDs) (3). The ED is a particularly promising venue for screening, brief intervention, and referral to treatment (SBIRT), as it is the portal into mental health services for most suicidal patients (4). While many suicidal patients present to the ED following suicide attempts, other patients at risk for suicide go unrecognized, and therefore untreated, in the ED (3). Once discharged, 30% of suicidal patients return to the ED with another crisis within six months of the sentinel event (5). The Joint Commission recently issued a Sentinel Event Alert recommending routine SBIRT in the ED to prevent suicide in “unknown at risk” patients. However, evidence-based guidelines for screening and intervention programs do not exist (6), highlighting the significance and timeliness of research aimed at improving care for patients in the ED who are identified as being at risk for suicidal behavior.

This proposal aims to study a novel treatment engagement intervention for youth who screen positive for elevated suicide risk on a standardized screening tool while presenting to the ED with non-psychiatric complaints. This two-site study (Cincinnati and Nationwide Children’s Hospital Emergency Departments) will enable efficient and timely recruitment of a diverse sample of high risk adolescents.

## **PURPOSE**

This two-site study tests the effectiveness of a brief treatment engagement intervention termed Suicidal Teens Accessing Treatment after an ED Visit (STAT-ED) for adolescents seeking treatment in the ED for non-psychiatric concerns but identified via systematic screening as being at risk for suicide. In this 3-year proposal, investigators from two institutions (Cincinnati Children’s Hospital Medical Center [CCHMC] and Nationwide Children’s Hospital [NCH]) will recruit and randomize 160 adolescents (80 per site) to (a) the STAT-ED intervention or (b) enhanced usual care (EUC) as a comparison condition. EUC consists of a brief consultation and a mental health referral. The STAT-ED intervention targets family engagement, problem solving, motivational interviewing, assistance with referral and limited case management during the transition from the ED to outpatient care with the goal of maximizing the initiation of mental health treatment and aftercare among youth screening positive for previously unrecognized suicide risk.

The primary aim of this study is to test the following two hypotheses:

1. Adolescents receiving the STAT-ED intervention will have a significantly higher rate of initiating mental health treatment and will attend more mental health treatment sessions in the two months after the ED visit compared with adolescents in the EUC condition.
2. STAT-ED will be superior to EUC in reducing suicidal ideation and depression symptoms at two months and six months.

Secondary aims are exploratory and designed primarily to provide estimates of effect size for future larger-scale investigations:

1. Determine whether the effectiveness of the STAT-ED intervention differs by age, gender, or ethnicity.
2. Evaluate predictors and mediators of mental health treatment engagement. We hypothesize that mental health treatment engagement in both arms will be predicted by higher clinical suicide severity, lower family barriers to treatment, and lower service access barriers. High scores in the action stage of change will predict successful mental health treatment engagement, in general, but particularly for those enrolled in STAT-ED.

This study is based on a pilot study performed in the CCHMC ED called “An Assessment of Voluntary Adolescent Mental Health Screening and Referral in a Children’s Hospital Emergency Department” ID-2008-0987 which screened over 200 adolescents and randomized 24 to receive either the TeenScreen-ED intervention, the forerunner of the current intervention, or enhanced usual care (EUC). This study received a full ORCRA audit without findings.

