### **Sample Size Justification**

Power analyses. All power calculations are for 2-sided tests,  $\alpha=0.05$ , and require power of 80%.

The primary outcome of mental health treatment initiation used in the sample size calculation is the proportion of participants who have attended at least one mental health visit in the 2 months after the ED visit, as assessed by the independent evaluator and verified with the mental health provider. Using a  $\chi^2$  test of proportion with continuity correction, power estimates for detecting differences in rate of treatment initiation during follow-up in the intervention and control group were computed using an expected rate of treatment initiation of 50% in the EUC arm. Under this assumption, the study will require 66 patients per treatment group to detect an intervention effect of 50% improvement in mental health treatment initiation (Table 4). We increased the number of participants to 80 per group to account for possible attrition and the chance of a lower rate of treatment initiation in the EUC group. With regard to the number of overall outpatient treatment sessions attended during follow-up, with 80 participants in each group, we are able to detect a difference in mean number of visits of between 1.7 and 2.2 (98). These calculations were based on an expected standard deviation  $\approx$  4.0-4.5 visits obtained from data reported by Spirito (34), Rotheram-Borus (33), and Asarnow (35).

On the basis of prior work, we anticipate retaining over 85% of participants for repeated assessment. For the primary aim, we will use an intent-to-treat analysis (ITT), and hence retain all 160 subjects. We will monitor the reasons for withdrawal, and use sensitivity analysis with missing data methods to assess the effects of withdrawal.

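### The primary aim covers six comparisons, but treatment initiation alone is called the primary outcome and sets the sample size, and the protocol does not say which results meet the aim

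*Protocol*

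**What the plan says.** Protocol, PURPOSE: "The primary aim of this study is to test the following two hypotheses". Hypothesis 1 is that adolescents given STAT-ED "will have a significantly higher rate of initiating mental health treatment and will attend more mental health treatment sessions in the two months" that follow their attendance. Hypothesis 2 is that "STAT-ED will be superior to EUC in reducing suicidal ideation and depression symptoms at two months and six months". The secondary aims that follow are described as exploratory, so both hypotheses read as confirmatory.

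Protocol, Sample Size Justification: one outcome is singled out, "The primary outcome of mental health treatment initiation used in the sample size calculation", defined as at least one mental health visit within two months. The 66 per group comes from this outcome, using "an expected rate of treatment initiation of 50% in the EUC arm" and a 50% improvement. The section also gives a detectable difference of 1.7 to 2.2 visits for sessions at 80 per group. It gives nothing for ideation or depression. The error level is introduced by "All power calculations are for 2-sided tests" at 0.05.

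Protocol, DATA ANALYSIS METHODS: an analysis paragraph is given for Hypothesis 1 (initiation and sessions). There is no matching paragraph for Hypothesis 2.

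**The concern.** The protocol assigns primary status in two places, and the two do not match. Under PURPOSE, six comparisons serve the primary aim. Under Sample Size Justification, one outcome is primary and the other five are not given that name.

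The difference matters when results are mixed. Suppose initiation shows no effect but depression at six months gives p<0.05. Under PURPOSE this could be reported as support for a primary hypothesis. Under Sample Size Justification the primary outcome has failed. A reader of the final report could not tell from the protocol which account was planned.

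Hypothesis 2 is also presented as confirmatory without any statement of the symptom difference that the trial could detect.

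**Working it through.** **Inputs.** From Sample Size Justification: two-sided 0.05, 80% power, 50% initiation under EUC, 50% improvement (read as 75% under STAT-ED), continuity-corrected chi-square, 66 required and 80 enrolled per group, session SD 4.0 to 4.5, retention over 85%. From PURPOSE: the list of comparisons. Assumed, because the protocol gives none: the success rule, the level for each test, and the correlations between tests.

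**1. The plan's own figure.** With p1 = 0.50, p2 = 0.75, mean 0.625 and difference d = 0.25, the uncorrected size is

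n' = [1.96·√(2·0.625·0.375) + 0.842·√(0.25 + 0.1875)]² / 0.25² = 57.7, that is 58.

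With continuity correction,

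n = (n'/4)·[1 + √(1 + 4/(n'd))]² = 65.4, that is 66.

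The stated 66 per group is reproduced exactly.

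**2. Which comparisons have a calculation.**

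| Comparison | Under the primary aim | Called primary outcome | Calculation given |
|---|---|---|---|
| Initiation, 2 months | yes | yes | yes, sets N |
| Sessions, 2 months | yes | no | yes, detectable difference |
| Ideation, 2 and 6 months | yes (two) | no | none |
| Depression, 2 and 6 months | yes (two) | no | none |

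For sessions, (1.96 + 0.842)·SD·√(2/80) gives 1.77 visits at SD 4.0 and 1.99 at SD 4.5. With 66 per group the values are 1.95 and 2.19. The stated 1.7 to 2.2 is therefore roughly matched across the two group sizes.

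**3. Family-wise error if any one of six tests at two-sided 0.05 counted.** Independent tests: 1 − 0.95⁶ = 26.5%. In the direction favouring STAT-ED only: 1 − 0.975⁶ = 14.1%, against 2.5% for one test. For correlated tests, equicorrelated normal statistics were simulated (1,000,000 draws).

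| Assumed correlation | Either direction | Favouring STAT-ED |
|---|---|---|
| 0 | 26.5% | 14.1% |
| 0.3 | 24.1% | 12.2% |
| 0.5 | 20.7% | 10.4% |
| 0.7 | 16.4% | 8.2% |

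**4. Other success rules.** If each hypothesis needed all its components, each would have error of at most 5%, so the two together at most 5% + 5% = 10%. If all six results were needed, error would not exceed 5%.

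**5. Detectable symptom difference.** The retention floor gives 0.85 × 80 = 68 per arm. In SD units, (1.96 + 0.842)·√(2/68) = 0.48 at 80% power, with no adjustment for covariates or multiplicity. A t-test calculation gives 0.484.

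**6. Cost of keeping all six as primary.** With Bonferroni, 0.05/6 = 0.0083 per test, and initiation alone would need 98 per group with continuity correction. The 80 planned would give about 68% power.

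**The case against.** Having one outcome drive the sample size does not rule out other primary outcomes, and Sample Size Justification does not say that initiation is the only one. On that view the labelling is unclear but not strictly contradictory. This is fair. The ambiguity remains, however, because the protocol never says how the six comparisons combine.

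Testing order and alpha allocation are commonly left to the SAP, which is not shown. Their absence is therefore not a fault here. Which outcome is primary is different: the protocol itself addresses it, in two ways.

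A reader might go further and infer the following. The document does not support these readings:

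- **That a false primary success is likely.** Even the worst case above is about 26%, and about 14% in favour of STAT-ED. Both need an any-one rule that the protocol does not state. Each hypothesis joins its components with the word *and*, which fits an all-components reading at least as well.
- **That each test is set at 0.05.** That level is stated for the power calculations. No per-test or family-wise level is fixed.
- **That only initiation was considered in sizing.** Sessions has a detectable difference. Only the symptom outcomes have none.
- **That six separate tests are planned.** Six comparisons are named, but no method is given for Hypothesis 2. One longitudinal model per symptom scale would also fit the text. With four tests the independent any-one figure would be 1 − 0.95⁴ = 18.5%.

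**Conclusion.** The point holds as a mismatch in what is called primary. Six comparisons sit under the primary aim, one outcome is named primary and sets N, and no rule says which results meet the aim. The four symptom comparisons have primary-aim status without any calculation.

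The effect on error depends on the success rule. It runs from no inflation if everything is required, through at most about 10% if each hypothesis needs all its components, to 16% to 26% if any one of six tests counts. The last range rests on an assumed rule, an assumed 0.05 per test, and assumed correlations from 0.7 down to 0. It shows what is at stake if the ambiguity stays; it is not the trial's stated error rate.

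The sizing for initiation is sound. This should be corrected, but it does not undermine the design.

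**What to change.** In PURPOSE, name initiation within two months as the single primary outcome, in line with Sample Size Justification. Relabel sessions attended and the whole of Hypothesis 2 as secondary, distinct from the exploratory aims.

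In Sample Size Justification, add the detectable symptom difference: about 0.48 SD at 80% power with 68 per arm, unadjusted.

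The cost is a change of wording in two sections. Initiation keeps the full two-sided 0.05, so 66 required and 80 enrolled per group stand. The downside is that sessions and symptom results lose primary status. A fixed testing order for the secondary outcomes is one option among several and may be left to the SAP.

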## **METHODS**

### **Study Design**

The proposed three-year, two-site study consists of the following: (1) Recruitment of 160 adolescents, ages 12-17 years inclusive at baseline, who screen positive in the ED for elevated suicide risk; (2) initial assessment of participants using direct interviews, standardized questionnaires, and parental/guardian informants; (3) randomization to either the STAT-ED intervention (n=80) or EUC (n=80) delivered in the ED; and (4) follow-up assessment of all participants at 2-months and 6 months post-baseline according to the protocol assessment schedule. See procedure section for additional detail.

### **Setting**

The proposed study will be conducted in the Emergency Departments at Cincinnati Children’s Hospital Medical Center and Nationwide Children’s Hospital.

### **Study Sample**

A total of 160 participants will be enrolled in the study, 80 at each site. 132 completed participants are required for data analysis purposes (see Data Analysis section for details). The N was increased to 160 to account for attrition and other factors that may affect completion rates.

Adolescents will be included in this study. This study presents no greater than minimal risk to the involved subjects (45 CFR 46.404). All procedures, including informed consent, will be conducted according to Good Clinical Practice to ensure the protection of this vulnerable population.

|                     |                                                                                                                                                                                                                                                                                                                                                                                                                                                                                                                                                               |
|---------------------|---------------------------------------------------------------------------------------------------------------------------------------------------------------------------------------------------------------------------------------------------------------------------------------------------------------------------------------------------------------------------------------------------------------------------------------------------------------------------------------------------------------------------------------------------------------|
| Inclusion Criteria: | 1. Patients who arrive in the ED who are between the ages of 12 and 17 years inclusive at time of consent;
2. screen positive on the Ask Suicide-Screening Questions (ASQ) tool(add the reference);
4. have had no contact with a mental health provider in the 90 days preceding the current ED visit.
5. Are stable as determined by vital signs and triage criteria (triage levels 3-5)                                                                                                                                                           |
| Exclusion Criteria: | 1. Patients who present in the ED with a chief complaint of suicidal behavior will be excluded to comply with the requirements of the RFA;
2. those who present in the ED with a primary or secondary psychiatric concern;
3. those without access to a telephone/cell phone;
4. those unable to adequately understand the study process;
5. those families unable to speak or read English adequately to participate in study procedures.
6. patients who have altered mental status either due to illness or medications (pain medications). |

## **PROCEDURE**

The proposed three-year, two-site study consists of the following: (1) Recruitment of 160 adolescents, ages 12-17 years inclusive at baseline, who screen positive in the ED for elevated suicide risk; (2) initial assessment of participants using direct interviews, standardized questionnaires, and parental/guardian informants; (3) randomization to either the STAT-ED intervention (n=80) or EUC (n=80) delivered in the ED; and (4) follow-up assessment of all participants at 2-months and 6 months post-baseline according to the protocol assessment schedule.

**Recruitment:** During study hours (we anticipate that this will be 5 to 10 PM, 7 days a week, but this may increase or decrease weekly as resources dictate), ED study staff will routinely offer a universal voluntary mental health screen to all medically stable adolescents aged 12-17 presenting with a custodial parent/guardian and with non-psychiatric complaints to the ED. Adolescents who screen positive on the ASQ and meet inclusion/exclusion criteria will be offered enrollment into the randomized control trial by trained research coordinators. In addition, all subjects at flight risk or imminent suicide risk will be treated as per the ED flight risk protocol. Subjects and families will be recruited according to IRB and Office for Human Research Protection (OHRP) guidelines. No research procedures will be performed prior to informed consent. After enrollment but prior to randomization, the Clinical Research Coordinator will give a brief description of the problems endorsed to the parent and adolescent and then conduct the baseline assessments. Once baseline surveys are complete, randomization will occur into either Enhanced Usual Care (EUC) or the STAT-ED intervention. If randomized into EUC, the adolescent will receive a psychiatric evaluation and a mental health referral from the ED psychiatric social worker. Because this is a study of high risk children, all adolescents in EUC will be evaluated by the ED psychiatric social worker as per their usual suicide risk assessment and be offered a referral, if clinically indicated. If randomized into the STAT-ED intervention, the adolescent and parent will receive a brief motivational interview, barrier reduction discussion, and referral and limited case management by the study social worker to enhance outpatient mental health follow up after discharge from the ED. This will include phone follow up to facilitate referrals, answer questions, help with barrier and logistical issues, until the first mental health follow up visit appointment date. Because by definition all adolescents in the study will be at risk for suicide, each will receive a full risk assessment while in the ED (by the study social worker in the intervention group or by the ED psychiatric social worker if in the EUC group). Study social workers will be trained to give full assessment of all suicidal patients as per the Psych ED suicide assessment protocol. These protocols (STAT-ED and EUC) were followed during the pilot study without complication. Adolescents thought to be at too high of risk to send home will be admitted and will continue to be followed in the study. No pilot study patients were severe enough to be admitted during the pilot study.

**Method for Randomization:** Participants will be randomized into the EUC or STAT-ED arm in computer generated blocks of 10 to the intervention and control groups. A computerized random number generator will be used to derive a list for randomization. Research staff performing follow up telephone surveys and data analysts will be blind to the participant's group allocation. A data analyst separate from the study statistician will generate a random sequence of numbers to be printed and placed in radio-opaque

envelopes with a sticker seal indicating the block in which the envelope is to be placed. Upon consent, the research social worker will take the next envelope, break the seal and determine whether the adolescent will receive the STAT-ED intervention or EUC thereby assuring allocation concealment.

**Two-Month and six Follow-up:** Mental health treatment engagement will be defined as the following: 1) treatment initiation, attendance at the first outpatient mental health follow up visit as reported by the family and verified by the mental health referral agency; and 2) overall attendance, mean number of outpatient mental health visits attended. Two month and six month post ED visit initiation and attendance, and assessment of suicidal ideation and depression will be ascertained via telephone contact with participants, parents and mental health agencies. This assessment will be performed by a research coordinator blind to treatment allocation. A HIPPA waiver will be obtained to allow a release of limited clinical data from the mental health referral. In the event that we are unable to contact the family to schedule the 2 month and 6 month phone follow up, the research coordinators will attempt to contact the alternate names provided by the family in order to make contact with the parent. If parents prefer to meet via a home visit or a location of their choice (for example a study office at the hospital or a neighborhood restaurant) study personnel will accommodate this request. In the pilot to the current study, we were able to contact the agencies for all 24 of the families to ascertain follow up compliance. Of the 24 patients randomized, 3 families were lost to follow up at 60 days. No families followed up with a mental health provider that was different than the initial ED mental health referral. All families who followed up did so within the first 6 weeks after the initial ED visit however we include an additional six month follow up phone call to ascertain symptom status. ED service use will be verified using the electronic medical record.

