#### **Variables to be Measured**

Please see uploaded instruments in appendix.

Under the leadership of [name] (Project Statistical Consultant), the team will use a variety of statistical methods to address the primary aims. Preliminary and descriptive analyses will inform subsequent analyses. Graphical representations will help identify aberrations, outliers, and missing data. Skewed data will be transformed or non-parametric approaches used when appropriate. We will start with basic methods, such as the comparison of rates of treatment initiation using chi-squared tests, and then proceed to analyses that may include adjustment for possible confounders and/or effect modifiers. Although we do not anticipate confounding due to an imbalance in covariates because of the RCT design, we will nevertheless test for differences in covariate distribution between study arms. If such imbalance is detected for specific covariates, we will introduce those covariates in the regression models. An indicator variable for site (Cincinnati, Columbus) will be included in all such models. We will use logistic regression models for the binary outcomes associated with initiation in mental health services. For analyses involving the number of follow-up visits, we assume a Poisson distribution. Accordingly, we will use Poisson regression models to assess differences in the number of follow-up visits between groups adjusted for potential confounders, if necessary. In all analyses, we will test for effect modification (interaction) by patient characteristics and study site. In the unlikely event that there is an interaction between study arm and study site, we will report site-specific results. We will use regression diagnostics to check our models for co-linearity and influential observations, using residual plots and associated quantitative methods.

Our primary analyses will compare STAT-ED and EUC using ITT analyses. Analysis by ITT requires that outcomes will be analyzed by randomization without regard to subject adherence to the study protocol. We will perform analyses to characterize participants who leave the study early relative to others.

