Hypothesis 1: STAT-ED will be superior to EUC in improving treatment initiation and overall treatment attendance. We will compare the rate of mental health treatment initiation in the STATED and EUC groups using the standard chi-square test of proportions. We plan to calculate effect sizes and confidence intervals in addition to simple tests of significance. As mentioned earlier, logistic regression models for adjustment will be used in the event of imbalance in any important covariates. We will compute the number needed to treat to benefit (NNTB) as an additional measure of the clinical significance of the impact of the STAT-ED intervention on treatment initiation rates relative to EUC. The analysis of overall number of treatment sessions attended by participants in each arm will use a likelihood ratio test based on the Poisson distribution. Similar to the analysis of treatment initiation, Poisson regression models will be used if covariate adjustment is necessary or for assessment of effect modification.

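### The protocol does not say that allocation is blocked within site, and the main test of treatment initiation leaves site out; the test stays valid, but some precision is given away

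*Protocol*

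**What the plan says.** - **Enrolment.** Study Sample plans 160 participants, 80 at each of two emergency departments.
- **Allocation.** Method for Randomization (under PROCEDURE) randomises "in computer generated blocks of 10" and adds: "A computerized random number generator will be used to derive a list for randomization". Results go into sealed envelopes marked with their block, and the research social worker opens the next one. Site is not mentioned in connection with the list, the blocks or the envelopes.
- **Main test.** The Hypothesis 1 paragraph compares initiation rates "using the standard chi-square test of proportions". Logistic regression is kept for the case where important covariates turn out imbalanced.
- **Sizing.** Sample Size Justification uses a chi-square "test of proportion with continuity correction", also without site.
- **Site in the models.** Variables to be Measured says of the covariate-adjusted regressions: "An indicator variable for site (Cincinnati, Columbus) will be included in all such models". Separately, it plans for all analyses a test of effect modification by site, with site-specific results if an interaction is found.

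**The concern.** Initiation means attending an outpatient mental health visit, confirmed by the referral agency. The two departments are in different cities, so initiation rates may well differ between them. The protocol recognises site as a factor in its regression models, but does not carry it into the one comparison on which the trial is sized.

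There are two consequences. First, balance of arms within site is not assured by the text, and the planned site interaction test and any site-specific results would benefit from that balance. Second, whether the main comparison of initiation is adjusted for site depends on a check made after the data are in. The interaction test is planned unconditionally, but it asks whether the effect differs between sites. It does not provide a site-adjusted test of the overall effect. What is at stake is precision and a clear advance choice of analysis.

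**Working it through.** **1. The plan's own figure.** Inputs from Sample Size Justification: "All power calculations are for 2-sided tests", alpha 0.05, 80% power, an "expected rate of treatment initiation of 50% in the EUC arm", and a 50% relative improvement, i.e. 75%.

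Uncorrected: n₀ = [1.96·√(2·0.625·0.375) + 0.8416·√(0.25 + 0.1875)]² / 0.25² = 57.7, so 58 per group.

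With continuity correction: n = (n₀/4)·[1 + √(1 + 4/(n₀·0.25))]² = 65.4, so 66 per group. The stated figure reproduces exactly and does not depend on how site is handled.

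**2. Balance within site under the two possible readings.**

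- *Blocks held per site.* 80 / 10 = 8 whole blocks, so 40 v 40 at each site at planned enrolment. If a site stops in mid-block, the arms there differ by at most 5.
- *One list used in arrival order across both sites.* The number on STAT-ED among a site's 80 has SD √(80⁴ / (160²·159)) = 3.17. In 40,000 simulated trials with blocks of 10, the difference between arms within a site had median 4 and 95th percentile 12 (46 v 34), and was 10 or more in 15.6%.

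A 46 v 34 split at one site (34 v 46 at the other) moves the crude arm difference in that trial by (46 − 34)/80 = 0.15 times the gap between site rates. That is 1.5, 3 and 6 points for gaps of 10, 20 and 40 points, against a target difference of 25.

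**3. Type I error and power.** The documents give no initiation rates by site, so these EUC rates are assumptions: 50/50, 40/60 and 30/70 (gaps of 0, 20 and 40 points). The effect for power is +25 points at both sites, with 80 per arm, complete outcomes and two-sided alpha 0.05. CMH is Cochran-Mantel-Haenszel stratified by site. Neither test is continuity-corrected; 40,000 trials per row.

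| Allocation | Site rates | Type I: chi-square | Type I: CMH | Power: chi-square | Power: CMH |
|---|---|---|---|---|---|
| One shared list | 50/50 | 4.8% | 4.9% | 91.3% | 91.2% |
| One shared list | 40/60 | 4.9% | 5.1% | 91.1% | 92.4% |
| One shared list | 30/70 | 4.7% | 4.8% | 91.0% | 95.6% |
| Blocks per site | 50/50 | 4.7% | 4.7% | 91.1% | 91.2% |
| Blocks per site | 40/60 | 4.2% | 4.6% | 91.6% | 92.6% |
| Blocks per site | 30/70 | 2.9% | 4.9% | 93.1% | 95.9% |

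With continuity correction on both tests the pattern is the same at lower levels. For a shared list at 30/70, power is 88.3% v 93.5%; with equal sites CMH gives up about 0.3 to 0.4 points.

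**4. Why per-site blocks make the chi-square conservative.** Under the null, the chi-square uses the pooled variance 0.5·0.5 = 0.25, but balanced sites leave only the within-site variance. That is 0.24 at 40/60 (0.4·0.6) and 0.21 at 30/70 (0.3·0.7). The effective critical value is 1.96·√(0.25/0.24) = 2.00, or 1.96·√(0.25/0.21) = 2.14. The normal approximation then gives type I errors of 4.5% and 3.2%. Simulation gives 4.2% to 4.4% and 2.9% to 3.1% across runs, in line with about 4.4% and 3.0%.

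**The case against.** The strongest reply is that nothing is invalid. An unadjusted chi-square is a legitimate primary test, it matches the sizing calculation, and power is near 91% in every row of the table, well above the 80% required. At a 20-point gap the gain from stratifying is only about 1 point, and the larger gains need a gap of 40. All of this stands, and it limits the point to an improvement.

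A reader might infer from the singular wording that one list is shared between the hospitals and that arms will therefore be unbalanced within site. The protocol does not say so. Physical envelopes marked by block, opened on the spot in two cities with no central allocation described, fit a shared arrival-order list poorly. Whole blocks divided between sites are at least as natural a reading. What remains is that the protocol states neither.

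A reader might also infer that a site difference could bias the arm comparison. Even under a shared list, a split such as 46 v 34 is chance imbalance. It is as likely to favour either arm, and the type I error already accounts for it (4.7% to 4.9%).

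Finally, it would be wrong to say that site is used only if imbalance is found, because the interaction test is planned regardless. If site itself came out imbalanced between arms, the covariate check could also bring in the logistic model with site. That softens the concern, but it leaves adjustment of the main comparison conditional on the data.

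**Conclusion.** The point holds as one of precision and clarity. The protocol does not state that allocation is blocked within site, and it fixes a main test of initiation without a site term. The chi-square is valid: about 5% type I error with a shared list, and conservative at about 4.4% and 3.0% with per-site blocks for gaps of 20 and 40 points. The loss against a site-stratified test is about 0, 1 and 3 to 5 points of power for gaps of 0, 20 and 40 points. The required 66 per group does not change.

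These sizes rest on assumed site rates, an equal 25-point effect at both sites, and complete outcomes on all 160. The documents do not support a claim of bias, of an underpowered trial, or of a list known to be shared.

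**What to change.** 1. In the Hypothesis 1 paragraph, name in advance a site-stratified primary test of treatment initiation: Cochran-Mantel-Haenszel by site, or logistic regression with arm and site. Keep the chi-square as a supportive analysis. The interaction test can stay as planned.
2. In Method for Randomization, state that a separate permuted-block list is generated for each site and that its envelopes are held there. At planned enrolment, 8 blocks of 10 give 40 v 40 per site. If this is already the practice, one sentence recording it is enough.

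The cost is two lists in place of one and a sentence in each section. No extra participants are needed, the sample size calculation stands, and if the sites turn out alike the loss of power is at most a few tenths of a point.
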